# 8. Data Collection

The primary investigator, [name], will be responsible for collection of these outcomes at baseline, after each subsequent menstrual period during the trial phase and then again at one, six and twelve months post trial completion.

Baseline data includes age, ethnicity, height, weight, age of menarche, onset of dysmenorrhea, length of menstrual cycle, length of menstrual period, smoking status, alcohol consumption, baseline analgesic usage and self reported dysmenorrhea symptoms and severity. A 5 point Likert scale will assess prior belief in acupuncture’s effectiveness.

*Primary outcome measure:*

Numerical rating scale (NRS) for pain. Each subject will keep a menstrual diary provided by the researcher. This will note the day of menses, average and maximum pain per day on an 11 point NRS with 0 being no pain and 10 being the worst pain imaginable. NRS is used in preference to VAS as it is comparable (59) but has a higher compliance rate, is easier to use and fits the compact format of a menstrual diary (60). The primary endpoint is a 20% difference in NRS rated average pain severity between groups.

*Secondary outcome measures:*

Secondary outcome measures which will be captured by the menstrual diary are duration of menstrual pain (hours), menstrual characteristics (flow, clots), painkillers taken (type, dosage, number of doses), non pharmacological interventions (heat,rest) and secondary symptoms of dysmenorrhea (headache, vomiting etc).

HRQoL will be recorded by the Short Form Health Survey (SF-36) at two time points; baseline and at the one month follow-up. The SF-36 has been shown to be valid and reliable across a range of populations (61,62) and has shown suitability for use in dysmenorrhea (63).

An exit questionnaire will be used to determine patient satisfaction with the different interventions and examine which components of the consultation and treatment sessions were important.

*Quality assurance:*

Quality assurance measures on needling technique and point selection will be carried out on practitioners during the study period by using an independent acupuncturist to check point selection and location at least once for each practitioner. Needling technique will be measured using a newly validated tool, the AcuSensor (64).

*In-depth interviews:*

These questions will focus on the participants experience in the trial and includes discussion on the therapeutic relationship, beneficial and negative aspects of the trial, explanation of TCM therapeutics and the provision of self-care/self help advice. These interviews will be recorded via a digital recorder.

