# 6. Investigational therapy and controls

## 6.1 Acupuncture

A total of 12 treatments over 3 menstrual cycles will be administered according to the frequency specified in the subjects’ group allocation. The study acupuncturists will include the primary investigator ([name]) and all study acupuncturists will be experienced, with a minimum of a Bachelors level qualification in Acupuncture and will hold a current annual practicing certificate with a relevant professional acupuncture body. Practitioners will be located in Auckland and Wellington, New Zealand. [name] will also be involved in training and quality control of other study acupuncturists.

Following the first phase of this mixed methods PhD thesis a trial protocol has been developed based around using a manualised version (50) of standard acupuncture treatments which has been designed in consultation with experienced practitioners through interviews and focus groups.

This manualisation allows considerable flexibility, in order that the treatment can match patient variability. The protocol is not too broad, such that “anything goes” as this would mean that it would be more difficult to attribute any impact of treatment to the different interventions we are using, frequency and stimulation of treatment. The protocol is also not too narrow, as we want the treatments to reflect how acupuncturists normally work in clinical practice. This is an important consideration in designing a clinically relevant intervention (25).

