## 7.2 Study assessments

The menstrual pain diary will be used to assess primary and secondary endpoints at baseline and at the end of every menstrual period during the 3 month study period. Follow-up pain diaries will also be collected at 1, 6 and 12 months post trial completion.

The SF-36 will be assessed at baseline and then at 1 month post trial completion.

Patient satisfaction with the trial will be assessed at the end of the trial with an exit questionnaire given after the final acupuncture treatment.

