# 10. Monitoring and quality assurance

## 10.1 Project management and trial management group

The primary investigator, [name], will have regular meetings with his supervisory panel and will discuss recruitment, compliance, retention and follow up as well as the implementation of the overall trial protocol. These meetings will also discuss any adverse event data reported by study acupuncturists.

[name] will also have regular email/phone conversations with other study acupuncturists to discuss any issues with recruitment, compliance, retention and follow up as well as the implementation of the overall trial protocol. In addition to this quality control will be undertaken at several points during the trial with each study acupuncturist being assessed at least once. Prior to the implementation of the protocol all study acupuncturists will be trained by the Primary Investigator and the AcuSensor device will be used to standardize needling technique to ensure that similar quality of stimulation is delivered by all study acupuncturists.

There is no data monitoring committee for this study.

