11.2.7 Data protection

All electronic files will be password protected. All paper files will be kept in locked filing cabinets at the home of the primary investigator, [name]

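### The primary investigator both treats women and collects their self-rated pain diaries, which leaves the uncontrolled before-after result, and possibly the between-arm contrast, open to reporting bias

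*Protocol*

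**What the plan says.** The protocol gives one person several roles.

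- **Treats.** Section 6.1: "The study acupuncturists will include the primary investigator".
- **Trains and checks the other therapists.** Section 6.1 says that the investigator "will also be involved in training and quality control of other study acupuncturists", and section 10.1 that "all study acupuncturists will be trained by the Primary Investigator".
- **Collects outcomes.** Section 8: the investigator "will be responsible for collection of these outcomes at baseline, after each subsequent menstrual period during the trial phase", and again at one, six and twelve months after the trial.
- **Keeps the paper records.** Section 11.2.7: "All paper files will be kept in locked filing cabinets at the home of the primary investigator".

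The outcome is self-rated. Section 8: "Each subject will keep a menstrual diary provided by the researcher", with pain scored daily from 0 to 10, and "The primary endpoint is a 20% difference in NRS rated average pain severity between groups". Satisfaction comes from "an exit questionnaire given after the final acupuncture treatment" (section 7.2).

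The arms in section 5.5.2 differ in visit pattern (three sessions in the week before menses, or one a week for three weeks) and in manual or electrical stimulation. Section 6.2 states that there is no control group. The protocol describes no blinding of women, therapists or outcome collection. The one independent check, in section 8, covers point selection and location. Section 10.1 says that there is no data monitoring committee.

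**The concern.** A pain score is easily coloured by who will read it. Here the reader is a therapist in the trial, for some women their own therapist, and knows those women's arm. Two results are exposed.

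1. **Objective 1 (section 2)** asks whether the manualised treatment gives a positive outcome. Without a control group this rests on change from baseline, so a wish to please the therapist counts directly as benefit.
2. **Objective 2 and the primary endpoint** compare frequencies and types of stimulation. They are distorted if women in one arm shade their ratings more than women in another, for example because they expect more frequent or electrical treatment to work better.

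Who receives the ratings is a matter for the protocol, and section 8 settles it. It is not a detail left to an analysis plan.

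**Working it through.** **Step 1: is the overlap real?** Yes. Sections 6.1 and 8 name the same role as therapist and as outcome collector, and no other section moves collection to someone who does not treat. That women and therapists know the arm is an inference from section 5.5.2 (the protocol does not use the word unblinded), but with these schedules and stimulation types it is a safe one.

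**Step 2: which result does a reporting shift affect?** Let the observed mean at factor level j be the true mean m_j plus a reporting shift r_j, and let r_0 be the shift in the baseline diary.

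- Before-after change = true change + (r_j − r_0). The baseline diary is completed before randomisation and treatment (section 5.2), so a shift that grows with the treatment relationship does not cancel.
- Between-level contrast = (m_1 − m_2) + (r_1 − r_2). A shift common to all arms cancels. Only a differential shift biases the contrast.

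If only women treated by the investigator shift, by s_j, and they make up a share p_j of level j, then r_j = p_j × s_j. The protocol gives neither p nor s.

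**Step 3: the plan's own scale.** Section 9.1 uses SD 1.3, alpha 0.05 and power 90% to reach 60 women, then 68 after 10% loss. The loss step reproduces: 15 / 0.9 = 16.7, so 17 per arm, and 4 × 17 = 68. The 60 cannot be reproduced uniquely, because the mean to which the 20% applies is not given. Taken as a two-sided main-effect comparison of 30 v 30, it corresponds to a difference of

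1.3 × (1.960 + 1.282) × √(2/30) = 1.09 NRS points.

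**Step 4: illustration of a differential shift b.** The values of b are assumptions and appear nowhere in the protocol. With no true effect, the standard error for 30 v 30 is 1.3 × √(2/30) = 0.336. The two-sided rejection probability is approximately

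1 − Φ(1.96 − b/SE) + Φ(−1.96 − b/SE).

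| b (points) | b/SE, 30 v 30 | Normal, 30 v 30 | t test, 30 v 30 | t test, 15 v 15 |
|---|---|---|---|---|
| 0 | 0 | 5% | 5% | 5% |
| 0.25 | 0.74 | 11.6% | 11.3% | 8.0% |
| 0.5 | 1.49 | 31.9% | 31.1% | 17.4% |

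A b of 0.25 would arise, for instance, if half the women at each level were treated by the investigator and those at one level alone shifted by 0.5 points: 0.5 × 0.5 = 0.25. That is 0.25 / 1.09 = 23% of the difference in step 3.

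**The case against.** The strongest reply is that the protocol says less than a reader might infer.

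- **Diaries handed over in person, or queried by the therapist.** Section 8 gives the investigator responsibility for collection. It describes no handover and no clarifying of entries. Information and consent can go by post (sections 5.2 and 11.2.1). The rating is self-completed, so the investigator does not score it. This stands: influence on entries is a possibility, not a stated procedure.
- **Every woman reporting to her own therapist.** Practitioners work in Auckland and Wellington (section 6.1), so this holds only for an unstated share. This stands.
- **A general wish to please biasing the primary contrast.** All four arms receive real acupuncture and 12 sessions, so a uniform shift largely cancels, and nothing shows that the investigator treats one arm more than another. This stands, and it limits the between-arm concern to differential reporting. It does not help objective 1.
- **A documented expectation favouring some arms.** Section 1.1 reports very positive results for higher frequency and for electroacupuncture, but calls the evidence conflicting and the studies methodologically poor. It makes a differential plausible and does not establish one.
- **Peripheral facts.** Home storage of paper files does not alter scores already written. The timing of the exit questionnaire does not say who hands it out or receives it. Neither adds much.
- **Partial mitigation.** Prior belief in acupuncture is recorded at baseline (section 8), and regression will examine factors influencing pain scores (section 9.2). That may help in interpreting a differential, but does not remove it.

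What survives is the core: a treating acupuncturist receives subjective ratings, and nothing in the protocol separates the two roles.

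**Conclusion.** The concern holds in a limited form. The overlap of roles is explicit. It leaves the before-after answer to objective 1 open to reporting bias. It leaves the between-arm contrast open to bias only if reporting differs by frequency or stimulation. Size and direction are unknown.

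A reader might take the 11% and 31% as estimates of the false-positive rate in this trial. They are not. They rest on assumed shifts of 0.25 and 0.5 points, the protocol's SD of 1.3 and a 30 v 30 comparison, and they show only that a differential well below the detectable difference would matter. Nor do the documents support a claim that the between-arm result is in fact biased. This is a modest weakness worth correcting because the avoidable part can be removed cheaply.

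**What to change.** In sections 7.2 and 8, state that:

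1. all post-randomisation diaries, the follow-up SF-36 and the exit questionnaire are self-completed and returned under Study ID by web form or in a sealed envelope;
2. women are told that no study acupuncturist, including the primary investigator, sees individual ratings until data lock;
3. the primary investigator receives only a list of forms returned or not returned, for reminders.

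The eligibility diary completed before randomisation can stay as planned, since allocation cannot affect it. The SF-36 requested at withdrawal (section 5.5.3) should follow the same route.

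**Cost.** A web form or prepaid envelopes, and one sentence for participants. No extra assessor is needed, because the forms are self-completed. If paper is used, someone who does not treat must open and enter the forms, and the protocol names no such person. Section 11.2.5 may place only the database backups at the university centre, so its capacity to receive forms should be confirmed, not assumed. Incomplete entries will be noticed later.

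**What remains.** Women will still know their schedule and stimulation type, and may still talk about pain during sessions. The protocol should state this as a limitation, above all for objective 1.

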# 9. Statistics and Data Analysis

## 9.1 Sample Size calculation:

This trial is designed to demonstrate a 20% difference in average pain intensity between groups as measured by the Numeric Rating Scale (NRS). Based on previous study data (65) a standard deviation of 1.3 units on a pain scale was used. An alpha of .05 and power of 90% gives a total sample size of 60 women. Previous studies (35,65) have had relatively low loss to follow-up (~10%) therefore a sample size of 68 women will be used to account for the predicted loss to follow-up of 10%.

## 9.2 Proposed Analysis:

For the data from the clinical trial a range of data analysis techniques will be undertaken including simple descriptive statistics; two way repeated measures ANOVA for NRS pain scores and SF-36 scores. Regression analysis with GLM will be used to examine factors influencing NRS scores, analgesic intake, secondary symptoms and non-pharmacological therapies. Non-parametric data such as analgesic intake, presence of secondary symptoms and usage of non-pharmacological therapies will be analysed by Mann-Whitney U-test.

Data from the in-depth interviews will be transcribed verbatim from the digital recording by the researcher. NVIVO will be used to manage the transcribed data and digital recordings. Thematic analysis will be used to identify emergent themes from the data.

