# 2. Study Objectives

The primary aim of this project is to examine the effect of changing frequency and type of stimulation on the symptoms of primary dysmenorrhea.

The specific questions that this project address are:

1. Does using a manualised protocol based on current clinical experience provide a positive outcome with symptoms of primary dysmenorrhea?
2. What extent do differing frequencies of treatment and types of stimulation contribute to that effect?
3. Is acupuncture, especially in more frequent treatments, an acceptable intervention for participants ?
4. Does TCM acupuncture change study participants perceptions of health and illness with respect to dysmenorrhea ?
5. What other components of the acupuncture treatment are important to study participants ?

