# 3. Study Design

A Phase III randomized controlled trial comparing 4 groups incorporating differing modes of stimulation and treatment frequency on pain and quality of life in women suffering from primary dysmenorrhea.

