# 4. Study Population

## 4.1 Sample Size

68 women in total, 17 participants per study group

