5.5.2 Treatment allocation

Randomization will be into one of four study groups:

High Frequency – Manual stimulation: Women randomly allocated to this group will receive 3 acupuncture treatments in the 7 days prior to menses and 1 acupuncture treatment in the first 3 days of menses. Stimulation will be provided by manual acupuncture, achieving DeQi upon needle insertion. Subsequent stimulation based on practitioners differential diagnosis. Needles will be retained for 20-30 minutes

High Frequency – Electro acupuncture stimulation: Women randomly allocated to this group will receive 3 acupuncture treatments in the 7 days prior to menses and 1 acupuncture treatment in the first 3 days of menses. Stimulation will be provided by Electro-Acupuncture, achieving DeQi upon needle insertion. Subsequent stimulation will be using a 2/100Hz waveform for 20-30 minutes.

Low Frequency – Manual Stimulation: Women randomly allocated to this group will receive 3 acupuncture treatments in the 3 weeks prior to menses (1/week) and 1 acupuncture treatment in the first 3 days of menses. Stimulation will be provided by manual acupuncture, achieving DeQi upon needle insertion. Subsequent stimulation based on practitioners differential diagnosis.Needles will be retained for 20-30 minutes

Low Frequency – Electro acupuncture stimulation: Women randomly allocated to this group will receive 3 acupuncture treatments in the 3 weeks prior to menses (1/week) and 1 acupuncture treatment in the first 3 days of menses. Stimulation will be provided by Electro-Acupuncture, achieving DeQi upon needle insertion.Subsequent stimulation will be using a 2/100Hz waveform for 20-30 minutes.

5.5.3: Withdrawal procedures

If a participant wishes to withdraw from the trial they will be immediately removed from treatment. The most recent menstrual pain diary will be used and they will be requested to complete an SF-36.

If a participant withdraws during intervention they will not be replaced however if they withdraw post randomization but prior to the first treatment they will be replaced.

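### Section 9.2 does not tie its named tests to the crossed frequency-by-stimulation design, and a baseline-adjusted factorial analysis would answer question 2 more directly and more efficiently

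*Protocol*

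**What the plan says.** Section 3 describes "A Phase III randomized controlled trial comparing 4 groups incorporating differing modes of stimulation and treatment frequency". Section 5.5.2 lists the arms: high or low frequency, each with manual or electro-acupuncture stimulation. The words factorial and 2x2 do not appear, but the four arms form that structure. Section 2 asks, as question 2, "What extent do differing frequencies of treatment and types of stimulation contribute to that effect".

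Section 7.2 has the pain diary assessed "at baseline and at the end of every menstrual period during the 3 month study period", and adds: "Follow-up pain diaries will also be collected at 1, 6 and 12 months post trial completion". Section 5.2 makes the screening diary the baseline for randomised women. The SF-36 is taken at baseline and one month after the trial.

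For the analysis, Section 9.2 names three things:

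- a "two way repeated measures ANOVA for NRS pain scores and SF-36 scores";
- GLM regression on factors influencing NRS, analgesic intake, secondary symptoms and non-drug therapies;
- "Non-parametric data such as analgesic intake, presence of secondary symptoms and usage of non-pharmacological therapies will be analysed by Mann-Whitney U-test".

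It does not name the two ANOVA factors, the role of the baseline diary, the GLM covariates, or the groups that Mann-Whitney compares.

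**The concern.** The design has three structural factors: frequency, stimulation and time. The named ANOVA is two-way. Which two factors it means decides what the primary analysis estimates, and the text allows several answers. With four groups by time, the test that comes out by default is an omnibus one. It can be significant without showing whether frequency, stimulation or their combination is responsible, and it spreads its degrees of freedom over patterns that question 2 does not ask about.

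Mann-Whitney takes two samples and one value per woman. Here there are four arms and a diary for every cycle. The same three outcomes are also given to GLM regression, with no statement of which result governs.

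At stake are a direct answer to question 2 and some power, in a trial expecting about 60 evaluable women.

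**Working it through.** **1. Sample size behind the check.** Section 4.1 gives "68 women in total, 17 participants per study group". Section 9.1 starts from 60 evaluable women and allows 10% loss: 60/0.9 = 66.7, so 67, and 68 as the next multiple of four. The dropout step reproduces. The 60 itself cannot be recomputed, because the 20% difference is not converted to NRS points. It would fit one factor compared 30 v 30 on a single unadjusted score at 1.3 × (1.960 + 1.282) × √(2/30) = 1.09 points, which is 20% of a mean of about 5.4. The check below needs only the 60: 15 per arm, so 30 v 30 for each factor.

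**2. Does a four-group-by-time ANOVA lose a factor?** No. The 3 df between groups split into 1 (frequency) + 1 (stimulation) + 1 (interaction). With baseline and three cycles, time has 3 df, and the 9 df of group-by-time split into 3 + 3 + 3. A numerical decomposition confirmed that the sums of squares add exactly. Both factors are in the model as contrasts. The omnibus test does not report them separately, and Section 9.2 does not specify them.

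**3. What is baseline adjustment worth, like for like?** Each comparison is the same 1-df frequency contrast, with and without baseline as covariate.

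Inputs: 30 v 30; SD 1.3 (Section 9.1), taken here as the SD of a single diary score. Assumptions, not in the protocol: equal correlation r between any two diaries, two-sided 5% level, and effects of 0.8 points (constant over cycles 1 to 3) or 1.1 points (at cycle 3).

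Variance factors v (multiples of SD²), for the mean of cycles 1 to 3:

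- post-treatment mean only: (1 + 2r)/3
- change from baseline: (1 + 2r)/3 + 1 − 2r
- ANCOVA: (1 + 2r)/3 − r²

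For cycle 3 alone: change 2(1 − r), ANCOVA 1 − r².

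SE = 1.3 × √(v × 2/30); power ≈ Φ(effect/SE − 1.96). At r = 0.5:

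| Contrast | v | SE | effect/SE | Power, normal | Power, t |
|---|---|---|---|---|---|
| Mean of cycles 1–3, effect 0.8, post-only or change | 0.667 | 0.274 | 2.92 | 83% | 82% |
| Same, ANCOVA | 0.417 | 0.217 | 3.69 | 96% | 95% |
| Cycle 3, effect 1.1, change | 1.000 | 0.336 | 3.28 | 91% | 90% |
| Same, ANCOVA | 0.750 | 0.291 | 3.78 | 97% | 96% |

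At r = 0.5 the post-only and change-score variances coincide.

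**4. How far does this depend on r?** Mean of cycles 1 to 3, effect 0.8, normal approximation:

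| r | v change | v ANCOVA | Ratio | Power post-only | Power change | Power ANCOVA |
|---|---|---|---|---|---|---|
| 0.3 | 0.933 | 0.443 | 2.11 | 90% | 69% | 95% |
| 0.5 | 0.667 | 0.417 | 1.60 | 83% | 83% | 96% |
| 0.7 | 0.400 | 0.310 | 1.29 | 76% | 97% | 99% |

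ANCOVA is at least as good throughout. Against the change score, the gain is largest when r is low; against the post-only mean, it is largest when r is high.

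**5. Mann-Whitney.** In a crossed design it can validly compare high with low frequency, or manual with electro stimulation. It has no place for a baseline covariate, takes one value per woman rather than one per cycle, and does not estimate the interaction. The GLM named in the same paragraph can do all three.

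**The case against.** Section 9.2 is a short outline and an SAP may exist, so naming factors and contrasts could be left to it. Several stronger readings that a reader might infer also go beyond the text:

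- **That a randomised factor is omitted.** Two-way may mean frequency and stimulation as between-woman factors with repeated measures, or group by time, which contains both factors (step 2). The defect is that the term is not tied to the design.
- **That the baseline diary is wasted.** Nothing excludes it. It may enter as a time level or as a GLM covariate, since GLM is planned for NRS too. The efficiency loss is conditional on how it is used.
- **That women with missing diaries are deleted.** Section 5.5.3 uses the most recent diary of a woman who withdraws. How an isolated missing diary is handled is not stated.
- **That six pairwise Mann-Whitney tests will be run.** No pairs are named; two comparisons, one per factor, are equally possible.
- **That the power loss is far larger than shown here.** Setting a 9-df omnibus test against a 1-df adjusted contrast gives a wider gap, but most of it comes from changing the hypothesis tested.

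It can also be said that GLM is meant to explore influences while Mann-Whitney makes the comparison, and that these outcomes are secondary. That is plausible, but the protocol gives neither analysis precedence.

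All of this narrows the point. It does not remove it: the tests the protocol itself names are not matched to its crossed design, and a better method is available from data already collected.

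**Conclusion.** The point holds as a mismatch between the named tests and the design, not as a proven error of omission. Section 9.2 does not say which two factors the ANOVA has. On the four-group-by-time reading with baseline as a time level, its omnibus result does not by itself answer question 2.

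The like-for-like gain from baseline adjustment is moderate: about 13 percentage points for a constant 0.8-point effect and about 6 for a 1.1-point effect at cycle 3, both at r = 0.5. The change-score variance for the mean of cycles 1 to 3 is 1.3 to 2.1 times the ANCOVA variance as r falls from 0.7 to 0.3. These sizes rest on the assumed correlation and effects; the protocol gives neither.

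Mann-Whitney is usable but incomplete, and overlaps with the planned GLM. The change should be made, because it costs little and serves the trial's main question.

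**What to change.** Revise Section 9.2 as follows.

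- **NRS pain:** a mixed model or ANCOVA with frequency, stimulation, their interaction, cycle and baseline NRS. Report the two main-effect contrasts, high v low frequency and manual v electro, with confidence intervals.
- **SF-36:** the one-month score with the same factorial terms, adjusted for baseline SF-36.
- **Analgesic use, secondary symptoms, non-drug therapies:** make the GLM already planned the single analysis, in place of Mann-Whitney. Use a family suited to counts or to yes/no data, the same factorial terms, baseline where it was collected, and clustering of cycles within woman.

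The cost is a change of wording, a little more analysis work and some reliance on model assumptions, which matters most for the count and yes/no models with about 60 women. No new data are needed: the baseline diary and baseline SF-36 are already collected.

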## 5.2 Screening for eligibility:

Initial screening will be undertaken over the phone by the researcher. Women who meet the eligibility criteria and are interested in joining the study will be met in person if they are located in Auckland or further information will be given via post or email if in Wellington. Prior to trial entry but post consent potential participants will be asked to fill in a menstrual pain diary that will be used to prevent recall error and validate that the participants do have maximum/peak pain greater than or equal to 3/10 and that this pain occurs just prior too, or in the first three days of menses. If these participants are eligible and are randomized then this data will become the baseline data.

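### The repeated-measures ANOVA in section 9.2 names no baseline adjustment: for SF-36 it must treat baseline as an outcome level, and for NRS pain either reading loses power against a baseline-adjusted comparison.

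*Protocol*

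**What the plan says.** Protocol section 9.2 names one method for both outcomes: "two way repeated measures ANOVA for NRS pain scores and SF-36 scores". It does not define the two factors, the time levels, or the term that carries the comparison of regimens. No baseline covariate is named. A separate sentence adds: "Regression analysis with GLM will be used to examine factors influencing NRS scores".

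The schedule is in section 7.2. For quality of life: "The SF-36 will be assessed at baseline and then at 1 month post trial completion". For pain, the diary is used "at baseline and at the end of every menstrual period during the 3 month study period", and "Follow-up pain diaries will also be collected at 1, 6 and 12 months post trial completion".

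Section 5.2 shows that the baseline diary is the screening diary, completed before allocation: "If these participants are eligible and are randomized then this data will become the baseline data". Section 8 gives the primary endpoint without a time point: "The primary endpoint is a 20% difference in NRS rated average pain severity between groups".

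**The concern.** A score recorded before randomisation cannot be changed by the regimen. If it is one of the outcome levels of a repeated-measures ANOVA, the group main effect averages in an occasion with no true difference. A steady effect after baseline then has to be found in the group-by-time term, which can spread it over several degrees of freedom. If the baseline score is instead left out of the model, the between-woman variation it could explain stays in the error term.

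The trial compares active regimens with no untreated control (section 6.2) and expects about 15 evaluable women per arm. With so few, a real difference between frequencies or stimulation types could be missed and reported as no difference. Every woman already supplies a baseline diary and SF-36, so the information is collected but not put to its best use.

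**Working it through.** **Inputs from the protocol.** SD 1.3 and 60 evaluable women (section 9.1); four arms of 17 (section 4.1). The dropout step reproduces: 60/0.9 = 66.7, or 68 in four equal arms. The 60 itself can be neither confirmed nor refuted, because the 20% difference is not given in NRS points.

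**Assumptions, not in the protocol.** Equal correlation ρ between occasions, 0.5 with a range of 0.3 to 0.7; a difference d between two pairs of arms, zero at baseline and constant afterwards; two-sided alpha 0.05. Power is from the noncentral F distribution.

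**SF-36: what the schedule forces.** With two occasions, an ANOVA of repeated measures needs baseline as a level. In SD units:
- The group main effect keeps 1/2 of the difference.
- Group-by-time (3 df for four groups) is the change-score test, with variance 2(1 − ρ) = 1.00 at ρ = 0.5.
- Analysis of covariance has variance 1 − ρ² = 0.75.

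For d = 1.0/1.3 = 0.77 SD, S = 60 × (0.769/2)² = 8.88. The noncentralities and power are:
- main effect: 8.88 × (1/4)/0.75 = 2.96, about 25%
- group-by-time: 8.88/1.00 = 8.88, 67%
- covariance: 8.88/0.75 = 11.8, about 80%

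**NRS: both readings.** Take baseline plus three treated cycles and d = 0.8. Then S = 60 × 0.4² = 9.6 and σ² = 1.69. At ρ = 0.5:
- Baseline as a level, group main effect: 3/4 of the difference is kept and the variance is σ²(1 + 3ρ)/4. λ = 9.6 × 0.5625/(1.69 × 0.625) = 5.11 on 3 and 56 df.
- Baseline as a level, group-by-time: λ = 9.6 × 0.75/(1.69 × 0.5) = 8.52 on 9 and 168 df. If frequency and stimulation are modelled as factors, each factor-by-time term has 3 df.
- Baseline left out: variance σ²(1 + 2ρ)/3. λ = 9.6/(1.69 × 0.667) = 8.52 on 3 and 56 df.
- Baseline as covariate: variance σ²[(1 + 2ρ)/3 − ρ²]. λ = 9.6/(1.69 × 0.4167) = 13.6 on 3 and 55 df, or 1 and 55 df for one factor.

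| Power at d = 0.8 | ρ 0.3 | ρ 0.5 | ρ 0.7 |
|---|---|---|---|
| Group main effect, baseline a level | 54% | 42% | 35% |
| Group-by-time, 9 df | 33% | 46% | 73% |
| Post-baseline only, unadjusted | 76% | 65% | 56% |
| Baseline as covariate, four groups | 84% | 86% | 95% |
| Factor-by-time, 3 df | 51% | 67% | 89% |
| Baseline as covariate, one factor, 1 df | 94% | 95% | 99% |

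The first four rows are four-group tests and the last two are single-factor tests, so each should be compared only within its own set. Simulation (4,000 trials per scenario) agreed within about 2 points, with type I error of 4.3% to 5.2% for all tests.

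**Sensitivity to the effect, four-group tests, ρ = 0.5.** At d = 1.0, power is 62%, 69% and 85%, in the order of the table's first three rows, against 97% with the covariate. At d = 1.5 it is about 95%, 98% and above 99%, against above 99.9%. Baseline adjustment had the most power in every scenario tried.

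**The case against.** The strongest reply is that section 9.2 names a class of method and leaves occasions, covariates and the tested term to an analysis plan that is not shown. Section 7.2 is a collection schedule, and listing baseline in it does not make baseline an ANOVA level. For NRS this stands: no sentence says so. A reader might infer that the primary analysis certainly dilutes the regimen effect, but the documents do not support that. It is the natural reading, because one phrase covers both outcomes and section 7.2 lists baseline among the occasions at which the diary assesses endpoints. If baseline is left out instead, there is no dilution, only an unadjusted test. For SF-36 the reply fails, because two occasions leave no alternative.

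The GLM regression neither names nor excludes baseline. It might include it, but it is described as exploring influences on the scores, and nothing makes it the comparison of regimens.

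The 9 df are also open to challenge. The design crosses frequency with stimulation, and modelling those factors gives 3 df per factor-by-time term. That narrows the gap but does not close it: 67% against about 95% at ρ = 0.5.

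Nor does the ANOVA necessarily fall short of what was planned. A single-score comparison of 30 v 30 at SD 1.3 detects 1.11 points with 90% power, and the factor-by-time term detects 1.04 at ρ = 0.5 (1.24 at ρ = 0.3). The loss is therefore measured against the adjusted analysis, not against the sample-size statement.

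Finally, averaging the treated cycles is best only if the effect is constant. If benefit builds over the cycles, the average takes in early, smaller differences. That bears on the wording of the fix, not on the need to adjust.

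**Conclusion.** The point holds as one of efficiency. It is firm for SF-36: baseline must be an outcome level, and the usable test is a change-score test with error variance 1.00 against 0.75 at ρ = 0.5. For NRS it is conditional on how the ANOVA is set up, but each reading falls below the baseline-adjusted test.

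The size rests on the assumed correlation, the assumed difference and a constant post-baseline effect. It shrinks with a large difference, and for the group-by-time term also with a high correlation.

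Two stronger conclusions should not be drawn. The planned tests are not biased or invalid, since randomisation protects them. And spreading the effect over many degrees of freedom is not a description of SF-36, where the interaction has 3 df at most. This is also not a complaint about missing detail: the protocol states a method, and a better use of data already collected is available.

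**What to change.** In section 9.2, replace the repeated-measures ANOVA as the between-arm test with two sentences.

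- **SF-36:** analysis of covariance of the one-month score on the baseline score.
- **NRS pain:** a mixed model of the post-baseline diaries, with woman as a random effect and the baseline diary score as a covariate. It tests the frequency and stimulation effects (or the arm effect) at a cycle, or an average of treated cycles, stated in advance. Baseline is not an outcome level.

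The choice between one cycle and an average should be made by the sponsor before the data are seen, because section 8 gives no time point for the primary endpoint.

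The cost is one degree of freedom for the covariate in each model. No new data, visits or participants are needed.
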